**Methods:**

We are recruiting 350 high-risk men and 350 high-risk women across the country. Individuals are eligible, if they: (1) are 18 years or older, (2) have not had a depressive episode in the past two months, (3) are at high risk of MDE based on the MVRPs (predicted risk of 6.5% + for men and of 11.2% + for women), (4) can communicate in either English or French, and (5) agree to be contacted for follow-up interviews. The MVRPs were developed and validated using longitudinal data from over 10,000 Canadians across the country. Eligible participants are randomized into (1) the control group, and (2) the group receiving personalized depression risk information. The participants are assessed at baseline, 6 and 12 months regarding accuracy of risk perception, use of self-help strategies and changes in psychological distress and functioning. Qualitative interviews are conducted in sub-samples of the intervention groups to explore how the personalized information affects risk perception, self-help behaviors and mental health.

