### Recruitment

The target population for future preventive studies is high risk people in the general population. For the proposed study, we are recruiting eligible participants using the random digit dialing method (RDD). We have used the RDD for recruitment in other longitudinal studies [9, 10] and an ongoing national RCT [11]. Recruitment, screening, baseline assessment and randomization are completed by a telephone survey firm that has access to household telephone and validated cell phone numbers across the country. The recruitment and randomization procedures and questionnaire were pilot tested in 20 eligible participants, using a cognitive interviewing method [12].

A random sample of landline and cell phone numbers are selected. When a household is reached, the person who is 18+ years is assessed for eligibility. If a household has 2+ persons aged 18+ years, one is randomly selected. The interviewers explain the study objectives and procedures and answer questions. Potential participants are ensured confidentiality, that participation is voluntary and that they may withdraw at any time. Oral consent is obtained before assessment of eligibility by asking the question: “Do I have your consent to begin the survey?” The answer of “yes” and continued participation is deemed to be informed consent. The Research Ethics Board formally approved this consent.

Outcome measures are assessed at baseline, 6 and 12-month.

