#### Perception of depression risk is assessed by asking

“How likely are you to get depression in the next 4 years?“ [13, 14] The answer can range from 0 to 100, where 0 = certain not to happen and 100 = certain to happen [13, 14].

*Self-management strategy use scale (SSUS)* was developed and validated by Morgan and Jorm [15]. The.

SSUS assesses the frequency of using each of the 14 self-help strategies [15], including strategies supported by research evidence (e.g., physical exercise,20–23 mindfulness relaxation,24;25 and online cognitive behavior therapy [16, 17]). Frequency of use can be rated on a 5-category scale. The SSUS has good internal consistency (Cronbach’s a = 0.80) [15].

*The Non-Specific Psychological Distress (K10)* is a 10-item screening scale intended to yield a global measure of distress based on questions about anxiety and depressive symptoms that a person has experienced in the most recent 4 week period [18]. The scale strongly discriminated between community cases and non-cases of DSM-IV disorders, with areas under the Receiver Operating Characteristic curve of 0.87–0.88 for disorders having Global Assessment of Functioning (GAF) scores of 0–70 and 0.95–0.96 for disorders having GAF scores of 0–50.28 We will compare the changes in the K10 scores over time between the groups to assess whether disclosing the personal risk leads to more psychological distress.

*Functioning impairments* is assessed by the question asking how the symptoms in the K10 affect functioning at home, work and school. We will also ask participants their number of days off work due to health problems in the past month.

*Sex-specific MVRPs for MDE* are administered to identify individuals who are at high risk for MDE, determine eligibility and assess accuracy of *perception of depression risk* over time. The algorithms have good discrimination (C statistic of 0.76 for women and of 0.79 for men), which is consistent with the range of C statistics of risk algorithms (0.75–0.80) in cardiology [19].

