#### Baseline assessment

In eligible participants, the interviewer administers the K10, SSUS, and asks questions about absenteeism and perceived risk of MDE. Baseline assessment takes 20 to 25 min.

*Randomization* is carried out in men and in women. The telephone survey firm uses a survey software tool built by Voxco. The tool contains a random number generator which randomly creates a digit when the telephone script reads the function. The firm confirmed that this is comparable to the traditional method of using sealed opaque envelopes.

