### Statistical analysis

All analyses will be carried out in men and in women separately, and by group assignment. We will perform an intention-to-treat analysis based on randomization. Each outcome will be analyzed with a separate regression model that includes intervention assignment and demographics, history of MDE and predicted risk at baseline as covariates.

Mixed ANOVA with a random intercept will be used to examine the effect of disclosing personalized depression risk information on changes in the SSUS scores, K10 scores and number of days off work. The mixed model will enable the repeated measures to be included in a single analysis and so that data from subjects not followed for the full year can be included. We expect no significant differences between the groups in changes of K10 scores and absenteeism at 6 and 12-month, i.e., disclosing the risk information does not lead to psychological and functioning harms. To examine the effect of risk disclosure on accuracy of perceived risk, we will first subtract participants’ perceived risk from the predicted risk. Positive values of the difference indicate underestimation of risk; negative scores indicate overestimation. We will recode difference scores into a dichotomous variable (≤10% vs > 10%) [13, 14], indicating whether perceived risk is “close” to the predicted risk. The proportions of accurate risk perception at baseline 6- and 12-month will be estimated and compared. Stratified analyses by demographic variables, history of MDE, baseline predicted risk levels will be conducted. Additionally, we will conduct the same analyses in participants who do not have missing outcome data (the completers).

Interim analysis will be conducted after 6-month follow-up. If the intervention group has a significantly higher incident proportion of major depression, and/or of suicidal behaviors, controlling for baseline covariates, than the control group, a team meeting involving staff of ethics review board will be held to review the results and determine whether the trial will be terminated.

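### The conclusion of no functioning harm rests on days off work alone, while a functioning question that applies to everyone is collected and plays no part in it

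*Protocol article*

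**What the plan says.** The Methods paragraph of the abstract lists among the assessed outcomes "use of self-help strategies and changes in psychological distress and functioning". The Recruitment section introduces the outcome list with "Outcome measures are assessed at baseline, 6 and 12-month". Within that list, functioning impairment has two items. The first is "assessed by the question asking how the symptoms in the K10 affect functioning at home, work and school". The second is "their number of days off work due to health problems in the past month".

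The Statistical analysis section applies the mixed model to effects "on changes in the SSUS scores, K10 scores and number of days off work". The authors expect no significant group differences in changes of K10 and absenteeism at 6 and 12 months, and gloss this as meaning that "disclosing the risk information does not lead to psychological and functioning harms". The same section also says, without naming any outcome, that each outcome gets its own regression model.

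The inclusion criteria (Methods/design) concern MDE status, age 18 or over, predicted risk, agreement to follow-up and language. Recruitment is by random digit dialing. Nothing restricts entry to people in work.

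**The concern.** The harm sentence draws two conclusions from two variables. K10 can support the psychological one. Only absenteeism is left for functioning, and absenteeism is defined only for people who have work to be absent from. A retired participant, a student or someone unemployed can deteriorate at home or in study without any change in days off work.

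The direction matters because the authors expect no difference and read it as reassurance. A measure that cannot respond in part of the sample pulls the comparison towards that expected result. The other functioning item, which asks about home and school as well as work, could respond in these participants, but the harm conclusion does not use it.

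**Working it through.** **1. The two sections side by side.**

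| Item | Listed as an outcome | Named in the mixed-model sentence | Used for the harm conclusion |
|---|---|---|---|
| K10 | yes | yes | yes (psychological) |
| Days off work | yes | yes | yes (functioning) |
| Home/work/school functioning question | yes | no | no |

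The functioning conclusion therefore has one input, days off work.

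**2. Figures in the plan.** The document gives no precision or sample-size figure for functioning or days off work. Its only calculation is for the SSUS: 258 per sex, raised for 75% response to 258 / 0.75 = 344, which reproduces. (The 258 itself does not follow from d = 0.40 at two-sided 0.05 and 80% power, which gives 99 per group and not 129. That is a separate matter with no bearing here.) Only the recruitment target, the 1:1 allocation and the 75% response are used below.

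**3. Dilution if non-workers are scored zero.** Let w be the share in work, similar in both arms by randomisation, and D the difference in mean days off among workers. Non-workers contribute zero in both arms, so

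overall difference = w × D + (1 − w) × 0 = w × D.

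The share in work is not in the document. Assuming 25%, 35% or 45% are not working:

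- w = 0.75: 75% of D
- w = 0.65: 65% of D
- w = 0.55: 55% of D

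**4. Loss of information if non-workers are missing.** Per arm per sex at 12 months: 350 × 0.75 / 2 = 131.25, about 131. The smallest standardised difference detectable with 80% power at two-sided 0.05 is (1.96 + 0.84) × √(2/n).

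| Assumed share not working | n per arm per sex | Detectable difference (SD) |
|---|---|---|
| 0% | 131 | 0.35 |
| 25% | 131.25 × 0.75 = 98 | 0.40 |
| 45% | 131.25 × 0.55 = 72 | 0.47 |

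These are simple two-group figures at one time point. They show the order of size, and they are not the power of the planned mixed model. Under either way of handling non-workers, those participants contribute nothing to the evidence on functioning.

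**The case against.** The best defence is the general sentence that every outcome gets a separate regression model. The functioning question is in the outcome list, so that sentence may cover it. The mixed-model sentence may name only numeric outcomes, and the response format of the functioning question is not given. A condensed article can leave such detail elsewhere. This stands to the extent that one cannot say the question will go unanalysed. It does not rescue the harm conclusion, which the article itself ties to K10 and absenteeism.

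The scoring of non-workers is also not shown. Zero and missing are both assumptions, and the skip pattern belongs in the questionnaire or SAP. That stands too, but neither rule lets days off work reflect worsening in someone without a job.

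Four stronger readings are tempting and are not supported:

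- A reader might infer that half of research question 2 would go unanswered. Question 2 in Methods/design asks about mental health status and is explained in terms of psychological distress. K10 addresses it for workers and non-workers alike. Functioning is a further outcome.
- A reader might infer that the functioning question was not asked at baseline, because that section says only that "the interviewer administers the K10, SSUS, and asks questions about absenteeism and perceived risk of MDE". That is a short list which also omits the demographic and service-use data collected at baseline. The question is tied to K10 symptoms and may be asked together with the K10.
- A reader might infer that days off work is a mere extra. Both items stand under one heading, and the text does not rank them.
- A reader might infer that illness-related job loss will be scored as improvement. No scoring rule in the document produces that, and no rate of job loss is given.

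**Conclusion.** The point holds in a limited form. As written, the analysis section concludes on functioning harm from absenteeism alone, although it has a second functioning item that is not confined to work. Because eligibility does not require employment, absenteeism cannot show worsening in part of the sample, and this favours the expected finding of no difference.

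The existence of the problem follows from the text and needs only some participants without a job. Its size does not follow from the text. Dilution to 75% to 55% assumes 25% to 45% not working and zero scoring. The fall from 131 to 98 or 72 per arm per sex assumes the same shares with those participants missing. The consequence is limited to the functioning conclusion. The K10 comparison, and the interim review of major depression and suicidal behaviour, do not depend on it.

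**What to change.** In the Statistical analysis section:

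1. Name the home/work/school functioning question as an outcome, analysed in all randomised participants at 6 and 12 months. Use a model suited to its response format and adjust for the baseline value where it was collected.
2. Base the statement about functioning harm on that outcome.
3. Keep days off work as a supporting outcome, analysed in participants working at baseline. Report by arm how many leave work during follow-up, if work status is available.

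The question is already described as collected, so steps 1 and 2 change only analysis wording. Step 3 needs work status at baseline. The socioeconomic data may contain it, but the document does not say so. The article reports baseline recruitment complete and expects 6-month interviews to finish by the end of September 2019, so a newly added work-status question might reach only the 12-month interviews. The downside is that one more outcome is tested and the days-off analysis covers fewer people.

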## Methods/design

Given the background, the aim of the proposed randomized controlled trial is to answer the following research questions: (1) Does disclosure of personalized depression risk information promote high-risk individuals to take preventive actions? The effect of risk prediction may be maximized if these individuals actively engage in early prevention. (2) Will disclosure of personalized depression risk information negatively affect high-risk people’s mental health status? To safely implement the prediction algorithms, we need to ensure that the disclosure will not lead to increased psychological distress.

This study is a mixed-methods randomized controlled trial (RCT) with an embedded qualitative component. The RCT has one intervention arm (receiving personalized depression risk information) and one control arm (1:1). The target population are individuals in the community who are at high risk of major depression. The personalized depression risk is generated using the sex-specific MVRPs for MDE that we developed in Canadians aged 18+ years old [4]. Thus, the inclusion criteria are:
no MDE at baseline, or if had a MDE in the past 12 months, the individuals were in full remission for at least 2 months before the interview (see below the question),aged 18+ years,at high risk of MDE based on the algorithms (predicted risk of 6.5% + for men and of 11.2% + for women) [4],agreement to be contacted for follow-up assessments, andno language barriers to English or French.

The status of remission was assessed by the question: “In the past 2 months or longer, has your mood been much improved or back to normal AND you DIDN’T have the symptoms of.....?” This question was adopted from the US National Epidemiological Survey on Alcohol and Related Conditions [7]. Because the prediction algorithms are sex-specific, we are recruiting 350 men and 350 women at baseline. After baseline assessment for eligibility, participants are randomized into intervention and control groups, in men and women separately.

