### Blinding and follow-up assessments

The telephone survey firm securely transfers encrypted baseline data to the PI on a weekly basis. The group assignment data are transferred in a separate file. The follow-up assessments are conducted at the telephone interview laboratory at the University of Ottawa Institute of Mental Health:
One month before the scheduled follow-up interviews, letters are sent to participants to remind them of the upcoming interview.After the 12-month interview, participants’ group status is linked with interview data by study ID numbers.

Investigators are blinded to participants’ group status. The interviewers who conduct randomization, are not involved in follow-up interviews. The interviewers who conduct the follow-up interviews in Ottawa do not have access to participants’ group status. Given our description of study objectives, participants may know their group status. Therefore, it is possible that some participants in the control group may try to find more information about personalized depression risk. At the follow-up assessments, we will ask if they have used any risk prediction tools over the study period. At the follow-up assessments, if participants develop a MDE, they are encouraged to contact family doctors and information about local mental health resources is provided.

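### The plan equates a non-significant difference in K10 change and days off work with absence of harm, without a margin or confidence-limit criterion

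*Protocol article*

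**What the plan says.** Methods/design sets the second research question as a safety question and gives its purpose: "To safely implement the prediction algorithms, we need to ensure that the disclosure will not lead to increased psychological distress". The outcome descriptions make the between-group comparison of K10 change the instrument for this, "to assess whether disclosing the personal risk leads to more psychological distress".

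Under Statistical analysis, K10 and days off work go through the same random-intercept mixed ANOVA as the SSUS, in men and women separately. The stated interpretation begins: "We expect no significant differences between the groups in changes of K10 scores and absenteeism at 6 and 12-month, i.e., disclosing the risk information". The sentence then completes the equation by saying that such disclosure "does not lead to psychological and functioning harms". The article gives no other criterion for answering the K10 and absenteeism question.

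Sample size calculation rests on the SSUS alone: a standardised effect of 0.40, power 0.80, alpha 0.05, 129 per group, 75% response at 12 months, and 350 recruited per sex. No power is stated for K10 or absenteeism.

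**The concern.** A difference test can show harm. When it fails to reject, it does not show that harm is absent. The words that join the two halves of the sentence treat the second as a restatement of the first.

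The consequence runs the wrong way for a safety question: the less informative the comparison, the easier it is to reach the reassuring conclusion. Attrition, a noisy scale or controls who look up their own risk would each make non-significance more likely. The Background says stakeholders want this question answered before implementation, so a false reassurance would bear directly on that decision.

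**Working it through.** **Inputs.** 350 per sex, 1:1 allocation and 75% response come from Methods/design and Sample size calculation. Alpha is 0.05; the article does not say whether it is two-sided, and two-sided is assumed. No K10 SD or correlation between visits is given, so effects are in SD units over an assumed range.

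**The plan's own figure.** For the SSUS, n per arm = 2(1.96 + 0.842)² / 0.40² ≈ 98.1, so 99, not the stated 129. The stated 129 fits an effect of 0.35 at 80% power, or 0.40 at about 89%. The attrition step does reproduce: 258 / 0.75 = 344. The gap is a separate matter and slightly helps the safety comparison. Neither figure addresses K10.

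**Precision per sex.** Evaluable per arm: 350 / 2 × 0.75 = 131. Standard error: √(2/131) = 0.1236 SD. 95% CI half-width: 1.96 × 0.1236 = 0.24 SD. An estimate just short of significance, near 0.24 SD, would have an upper limit near 0.48 SD, and the sentence would still read it as no harm.

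**Chance that real harm is non-significant.** Power ≈ Φ(d / 0.1236 − 1.96); miss rate = 1 − power. If harm is equal in the two sexes and their results are independent, the chance that both are non-significant is the square of the miss rate.

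| True worsening | One sex missed | Both sexes missed |
|---|---|---|
| 0.20 SD | 63% | 0.634² = 40% |
| 0.25 SD | 48% | 0.475² = 23% |
| 0.30 SD | 32% | 0.320² = 10% |
| 0.40 SD | 10% | 0.101² = 1% |

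**Sensitivity.**
- No attrition (175 per arm): one-sex miss rates of 54% at 0.20 SD and 20% at 0.30 SD.
- Baseline adjustment, assumed correlation 0.5 to 0.7 (SD multiplied by √(1 − r²)), 131 per arm: 54% to 38% at 0.20 SD, and 20% to 8% at 0.30 SD.
- Change-score contrast (SD multiplied by √(2(1 − r))): no gain at r = 0.5; at r = 0.7, 45% at 0.20 SD and 12% at 0.30 SD.

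**What the sample could show under a margin rule.** With no true difference, the power to put the upper two-sided 95% limit below margin M is Φ(M / 0.1236 − 1.96). Per sex, at one time point, unadjusted, this is 53% at 0.25 SD, 68% at 0.30 SD and 81% at 0.35 SD.

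**The case against.** The sentence opens as an expectation. It can be read as a hypothesis rather than a decision rule, and the mixed model will yield an estimate and interval in any case. That is fair as far as it goes: the article does not say that a null result will be taken as proof. It does say what a null result would mean, and offers no other criterion for these outcomes. A statistical analysis plan that is not shown might set a margin. The objection is to the stated equation, which would still need correcting.

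The calculation is also simpler than the planned analysis, which uses repeated measures, covariates and partly followed participants. This stands, and the sensitivity figures show how far it could matter.

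Four stronger readings are tempting but not supported:
- A reader might take 63% as the share of trials that would miss a 0.20 SD harm. It is a rate within one sex. Each trial gives two K10 results, and both would be non-significant about 40% of the time.
- A reader might infer that harm before month 6 is never compared between arms. That is true of K10 for most of the period, since it covers what "a person has experienced in the most recent 4 week period" and is first repeated at 6 months. But the interim analysis compares incident major depression and suicidal behaviours between arms after the 6-month follow-up. That check acts only on a significant excess, so it does not supply the missing K10 criterion.
- A reader might infer that contamination is recorded and then ignored. The article says "At the follow-up assessments, we will ask if they have used any risk prediction tools over the study period" and is silent on how the answers enter the analysis; silence in a condensed article does not show neglect. Nor does that question clearly establish who knew their own risk, so it is a weak basis for a contamination-adjusted estimate.
- A reader might conclude that the sexes should be pooled for the safety answer. The trial is sized and analysed by sex, and precision alone is not a reason to overturn that.

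**Conclusion.** The point holds as an error of inference in the Statistical analysis section: non-significance is equated with no harm, for a question whose purpose is to rule harm out. The logical fault does not depend on any calculation. Its practical size depends on how large a harm matters. Small harms (0.20 to 0.25 SD) would be missed in roughly half to two thirds of single-sex comparisons, while a 0.40 SD harm would be missed in about one in ten. These figures assume 131 evaluable per arm, a two-sided 0.05 test, one time point and no variance reduction, and they would fall if the planned model gains precision. The documents give no K10 SD, so none of this can be put in K10 points.

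**What to change.** Replace the sentence with a rule such as this: for each sex, no material increase in distress is concluded only if the upper limit of the two-sided 95% CI for intervention minus control in K10 change lies below a margin in points; otherwise the estimate and CI are reported without a no-harm claim.

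- The team chooses the margin before any between-group outcome comparison. Waiting for the group linkage after the 12-month interview would be too late, because the 6-month interim already compares the arms.
- Handle days off work the same way, or report its CI only.
- State the power for the chosen margin. The per-sex figures above are for one time point; requiring success at both 6 and 12 months would lower them.
- Word the K10 conclusion as distress in the 4 weeks before the 6- and 12-month interviews, not all distress after disclosure.
- A pooled, sex-stratified estimate may be added as supportive, not as the lead result. With 262 per arm its power is about 82% at 0.25 SD and 93% at 0.30 SD, at one time point.

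The cost is a change of wording, one margin decision (two if days off work gets its own) and a power statement, with no new data. The downside is that a no-harm claim becomes harder to make, and at margins below about 0.35 SD the single-sex comparisons may well be inconclusive.

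### The accuracy outcome for risk perception applies a one-sided cut to a signed difference, so as written every overestimator counts as accurate

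*Protocol article*

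**What the plan says.** The definition is in the Statistical analysis section of the protocol article. To assess accuracy, "we will first subtract participants’ perceived risk from the predicted risk". The sign is then given a meaning: "Positive values of the difference indicate underestimation of risk; negative scores indicate overestimation". The following sentence sets the cut: "We will recode difference scores into a dichotomous variable (≤10% vs > 10", in per cent, with two citations, and describes the result as "indicating whether perceived risk is “close” to the predicted risk". The planned use is: "The proportions of accurate risk perception at baseline 6- and 12-month will be estimated and compared".

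Two other statements fix the possible range of the score. For the perceived-risk item, "The answer can range from 0 to 100, where 0 = certain not to happen and 100 = certain to happen". The inclusion criteria under Methods/design require "predicted risk of 6.5% + for men and of 11.2% + for women".

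**The concern.** Closeness is a two-sided idea: a perception can miss by being too low or too high. The protocol recognises both errors when it explains the sign, but the cut that follows has only an upper limit. A score of -50 satisfies the condition of being at most 10 just as a score of 0 does.

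Disclosure can improve perception by raising estimates that are too low or by lowering estimates that are too high. The rule as written sees only the first. It would also miss, or even reward, a shift into gross overestimation after disclosure. That matters in a trial that asks whether disclosure harms mental health.

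**Working it through.** The protocol gives no figure for this outcome, so there is nothing to reproduce. The check is to apply the rule to every possible answer.

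**Inputs.** Score D = predicted − perceived (Statistical analysis). Perceived risk runs from 0 to 100 (perceived-risk item). Entry floors are 6.5% for men and 11.2% for women (Methods/design). The other predicted risks below are illustrative. The 10% is read as percentage points, because D is a difference of two percentages.

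**Rule as written:** inaccurate if D > 10. **Absolute rule:** inaccurate if |D| > 10.

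**Step 1, overestimators.** If perceived > predicted, then D < 0, so D ≤ 10 and the person is scored accurate. Example: 6.5 − 100 = −93.5, scored close.

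**Step 2, the ceiling.** D is largest when perceived = 0, where D equals the predicted risk. If predicted risk is 10 or less, D ≤ 10 for every answer. At entry this covers men from 6.5% to 10%. It covers no women, since 11.2 > 10. A woman at 11.2% is inaccurate only if perceived < 11.2 − 10 = 1.2, that is, if she answers 0 or 1.

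**Step 3, enumeration over the 101 whole-number answers.**

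| Predicted risk | Inaccurate, as written | Inaccurate, absolute rule |
|---|---|---|
| 6.5% (men's floor) | 0 | 84 (17–100) |
| 8% (men) | 0 | 82 (19–100) |
| 10% (men) | 0 | 80 (21–100) |
| 11.2% (women's floor) | 2 (0–1) | 81 (0–1, 22–100) |
| 15% | 5 (0–4) | 80 (0–4, 26–100) |
| 25% | 15 (0–14) | 80 (0–14, 36–100) |
| 40% | 30 (0–29) | 80 (0–29, 51–100) |

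At none of these predicted risks is an overestimating answer scored inaccurate by the rule as written. The counts are of possible answers. They are not estimates of how many participants would give them.

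**Step 4, effect on change over time.** Take predicted risk 25%, with perceived risk moving from 5 to 80. D goes from 25 − 5 = 20 (inaccurate) to 25 − 80 = −55 (accurate). The rule records an improvement although the absolute error has grown from 20 to 55. Take predicted risk 8%, with perceived risk corrected from 60 to 8. D goes from −52 to 0, accurate both times, so the correction is invisible.

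**The case against.** The strongest reply is that an absolute difference was plainly meant. The variable is introduced as a measure of closeness, the next sentence calls it accuracy, and the sign convention treats overestimation as an error. This is persuasive as to intent, and a reader should not infer that the investigators want overestimators counted as accurate. But it does not cure the text. An analyst who follows it has a signed variable and a one-sided cut, and the cited sources are not available here to settle the coding. Nor is this a detail left to another document: the rule is stated, and it conflicts with its own description.

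Three further objections stand and limit the point.

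- Under the absolute rule, a man at 6.5% to 10% who answers 0 still counts as close. It is tempting to call that a second error, but it is simply what a 10-point margin means. The protocol already plans stratified analyses by baseline predicted risk, which can show it.
- It is tempting to infer that most participants would be misclassified, or that the baseline proportion would sit near 100%. The document gives no distribution of predicted or perceived risk. For example, if men's predicted risk were 6.5% plus an exponential tail with mean m, the share at or below 10% would be 1 − exp(−3.5/m): about 58%, 35% and 21% for m = 4, 8 and 15. Nothing in the document chooses among these.
- The two research questions concern preventive actions and mental-health harm, and the sample size rests on the self-management strategy score. Perceived risk is collected on its raw scale, so nothing is lost that recoding cannot recover.

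**Conclusion.** The definition is wrong as written and should be fixed before analysis. Two consequences follow exactly from the text: all overestimators are scored accurate, and men with predicted risk of 6.5% to 10% cannot be scored inaccurate whatever they answer. The second depends on reading 10% as percentage points; on a relative reading it would not follow, but the first would. The 11.2% floor protects women at entry only. If predicted risk is re-estimated at follow-up, the second consequence applies to anyone then at 10% or below.

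The number of participants affected cannot be derived from the document. The findings on the trial's two research questions are not at risk. What is at risk is the meaning of a planned outcome and of any comparison of arms on it.

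**What to change.** Define accurate perception as |predicted − perceived| ≤ 10 percentage points. Fix this before group status is linked to outcome data, including any linkage needed for the interim analysis after the 6-month follow-up. Report by arm, at each assessment, the proportions underestimating by more than 10 points, within 10 points, and overestimating by more than 10 points. The three-way split keeps the direction of error, which the binary variable discards.

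Optionally, add the continuous absolute difference as a supportive analysis, leaving the cited dichotomy in place. When presenting the planned stratification by baseline predicted risk, note that under the absolute rule men at or below 10% can be inaccurate only by overestimating.

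The cost is one line of definition and one extra table. Both risks are already part of the planned data, so no further collection is needed.
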